### Relevant concomitant care permitted or prohibited during the trial {11d}

Participants consuming medications other than antiepileptics and benzodiazepines will be allowed to continue to consume them. No change in medications is required to participate in the study. Any medication taken during the study will be recorded in the eCRF (anamnestic module of the Qualtrics survey). Participants with an ongoing treatment with antiepileptics and benzodiazepines will be excluded from the study.

### Provisions for post-trial care {30}

If the participant is withdrawn due to an adverse event, the investigator will arrange for follow-up visits or telephone calls until the adverse event has resolved or stabilized. Eventual harm from trial participation will be covered by the Swedish ordinary patient injury insurance.

### Outcomes {12}

The primary outcome will be the change in negative emotional arousal from baseline, assessed immediately after the affect-induction procedure (post-induction ratings) using the PANAS. Negative emotional arousal will be measured through self-reported ratings of negative emotions on the PANAS (PANAS-N) at five time-points: baseline, after the neutral video, and after each of the three affect-inducing videos (designated as t1, t3, t4, t6, and t8 in Table 1). The means of the PANAS-N scores for each time point will be calculated and used to test the null hypothesis of no difference between the taVNS and sham taVNS groups. A mixed model analysis will be employed to assess each time point separately, ensuring comprehensive evaluation across all time points. The PANAS-N scores have already been used to measure the emotional arousal in previous studies using the same affect induction procedure with BPD patients and have been shown to be able to detect within and between groups differences [28]. The GSR recording, a physiological measure of emotional arousal, will be performed throughout the entire procedure and used to validate the PANAS-N data.

Since an increased emotional reactivity/intensity, one of the three components of the emotional vulnerability together with emotional sensitivity and longer emotional recovery time, is central in the physiopathology of BPD and the underpinning for many of the related symptoms and dysfunctional behaviors (e.g., self-harm) [5], to test the effect of taVNS on this primary outcome may have direct clinical utility. The available psychological treatments are associated with an improvement in the emotional regulation of BPD patients but have uncertain effects on the underlying emotional vulnerability [33].

The secondary outcomes of the study include:Change in negative emotional arousal from baseline at prior to affect induction (pre-induction ratings) as assessed by PANAS.Change in negative emotional arousal from immediately after affect-induction at 4 min after affect induction (recovery ratings) as assessed by PANASPerceived effectiveness in managing emotions (PEME) scores (0–9) during affect induction.

The change in negative emotional arousal from baseline at prior to affect induction measured through the PANAS-N scores has been included as a secondary outcome to test if taVNS can acutely reduce the baseline emotional arousal. It has been reported that BPD patients have higher resting-state emotional arousal levels, possibly explaining the elevated sensitivity to perceive emotion activation (i.e., emotion sensitivity) even with small emotional triggers [6]. The means of the PANAS-N scores taken at baseline (t1) and 4 min after the taVNS/sham taVNS has begun, before the affect induction procedure (t2) (pre-induction scores), will be used to test the null hypothesis of no difference between the taVNS and sham taVNS groups.

In the same way, the change in negative emotional arousal from immediately after affect-induction at 4 min after affect induction has been chosen to test the effect of taVNS on the third component of emotional vulnerability (i.e., slow return to emotional baseline). The emotional arousal will be measured through the PANAS-N at six time-points, i.e., immediately after (t4, t6, and t8) and at 4 min after each of the three affect-inducing videos (t5, t7, and t9). The means for the PANAS-N scores for each time point in which they are assessed will be used to test the null hypothesis of no difference between the taVNS and sham taVNS groups.

The last secondary outcome will be the PEME during affect induction. Participants will be asked during the postinduction period for each of the four videos (t3, t4, t6, and t8) about their perceived effectiveness in managing their emotions by asking them to rate “How difficult was it to manage your emotional response to this film clip?” from 1 = not at all to 9 = extremely. This scale will be interpreted as a subjective difficulty in regulating emotions in response to each video stimulus as done by Daros and coworkers [28].

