#### Self-reported rating measures

The primary outcome will be measured through the PANAS [27]. Before undergoing the taVNS and affect induction procedure, (“baseline” or t1), after 4-min taVNS and before the first video (“preinduction” or t2), and after each video (“postinduction” or t3, t4, t6, and t8), participants will be asked to provide affect ratings using the 20-item PANAS [27] (Table 1). The scale uses adjectives that describe mood states rather than discrete emotions and are rated from 1 = very slightly or not at all to 5 = extremely. The PANAS is used widely in mood induction procedures because of its good validity and test–retest reliability. At postinduction, participants provided self-report ratings on six basic emotions felt in response to each video (disgust, fear, anger, sadness, happiness, and surprise) on a scale from 1 = not at all to 7 = extremely. A total of 4 min after each negative video, participants provided another set of PANAS ratings to measure changes in mood over a longer period (“recovery” or t5, t7, and t9). The PANAS is a reliable and valid measure of the construct it is intended to assess [37].

Moreover, participants will be asked during postinduction about their perceived effectiveness in managing their emotions (PEME) by asking them to rate “How difficult was it to manage your emotional response to this film clip?” from 1 = not at all to 9 = extremely. This scale will be interpreted as a subjective difficulty in regulating emotions in response to each video stimulus.

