## Statistical methods

### Statistical methods for primary and secondary outcomes {20a}

This study constitutes a randomized trial employing repeated measures of a continuous outcome. To address the repeated measures within individuals as delineated by the inclusion criteria (specifically Swedish-speaking females aged 18-50 years diagnosed with BPD), and considering the attendant challenges of collinearity and intra-individual variability, mixed models with individuals as random effects will be employed across various stages of the study (baseline, pre-induction, post-induction, and recovery), as recommended by prior literature [76]. Covariates collected at baseline will be considered, with treatment group, treatment state, and time entered as fixed effects to estimate the effects stemming from the sham/intervention at each time point. The mixed model is versatile, accommodating both continuous and dichotomous outcomes, and will be utilized as deemed appropriate. Given the multitude of potential variables and outcome measures in this study, the necessity for adjustment for multiple tests may arise. To address the issue of multiple testing, we will consider applying the Bonferroni correction, which involves dividing the desired alpha level (typically 0.05) by the number of tests conducted. Alternatively, we may employ false discovery rate (FDR) correction methods to account for the increased risk of false positives when conducting multiple comparisons. The specific method chosen will depend on the final number and nature of outcome measures and variables included in the analysis and will be determined following the completion of the protocol.

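### The primary null is tested separately at several time points with correction left optional and no single primary contrast named, so an uncorrected false-positive rate of about 11% to 17% is permitted

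*Protocol article*

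**What the plan says.** Outcomes {12} opens with a clear variable: "The primary outcome will be the change in negative emotional arousal from baseline, assessed immediately after the affect-induction procedure (post-induction ratings) using the PANAS". It then says that PANAS-N is measured "at five time-points: baseline, after the neutral video, and after each of the three affect-inducing videos", that is, at t1, t3, t4, t6 and t8. The test is described as follows: "The means of the PANAS-N scores for each time point will be calculated and used to test the null hypothesis of no difference" between the arms. Then comes: "A mixed model analysis will be employed to assess each time point separately, ensuring comprehensive evaluation across all time points".

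Statistical methods {20a} describes mixed models with a random effect for the individual and with group, treatment state and time as fixed effects, used to estimate the treatment effect at each time point. On multiplicity it says that adjustment may become necessary, that "we will consider applying the Bonferroni correction", and that a false discovery rate (FDR) method is an alternative. The choice depends on which outcomes and variables are finally analysed and "will be determined following the completion of the protocol".

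Sample size {14} uses one calculation: effect size 0.25, power 0.8, alpha 0.05, two groups and four post-induction measures (neutral plus three negative videos). It gives 34, raised to 42 for attrition.

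**The concern.** The primary objective in Objectives {7} is a reduction in emotional reactivity. A reader of Outcomes {12} cannot tell which result decides whether that was shown. It could be a difference after any one video, after all of them, on average, or in a joint test. The neutral clip is in the same family, although Intervention description {11a} presents it as evoking very little emotion, so a difference there alone would not show reduced reactivity.

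Because correction is only to be considered, the text permits an analyst to report several unadjusted p-values and present the smallest as the primary result. This matters more here than in a double-blind trial: investigators know the allocation (Who will be blinded {17a}), and the research team also does the analysis ({5d}).

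**Working it through.** **1. The plan's own sample size.** I used the noncentral F distribution for repeated-measures ANOVA with f = 0.25, 2 groups, m = 4 measures, alpha 0.05 and N = 34. The correlation rho is not stated.

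- Group main effect: lambda = N f² m / (1 + (m−1)rho). With rho = 0, lambda = 34 × 0.0625 × 4 = 8.5 and power is 0.807.
- Group-by-time interaction: lambda = N f² m / (1 − rho). With rho = 0.26, lambda = 8.5 / 0.74 = 11.5 and power is 0.805.

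Attrition: 34 / 0.8 = 42.5, against 42 in the protocol. So 34 can be reproduced, but only as a single test at 0.05. It does not size an analysis made up of separate tests at each time point.

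**2. Chance of a false primary claim without correction.** If the tests were independent, the chance is 1 − 0.95^k: 18.5% for k = 4 and 14.3% for k = 3. Ratings from the same person are correlated, so I simulated two-sample t-tests with equal correlations, 17 per arm (34 / 2), no true effect and 20,000 runs. The correlations are assumptions.

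| Correlation | Four post-induction ratings | Three negative videos |
|---|---|---|
| 0.3 | 17.5% | 14.1% |
| 0.5 | 15.6% | 12.9% |
| 0.7 | 13.0% | 11.0% |

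A repeat with fresh random numbers agreed to about half a percentage point. Analysed as change from baseline, the figures are about 16% (four) and 13% (three), almost regardless of the correlation.

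**3. The same chance with a correction.** Four tests, 17 per arm, correlation 0.3 / 0.5 / 0.7:

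- Bonferroni (0.05 / 4 = 0.0125 per test): 4.7% / 4.2% / 3.5%.
- Benjamini-Hochberg: 4.8% / 4.4% / 3.9%.

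**4. Power, like for like.** Assumptions: d = 0.5 at each negative video (reading f = 0.25 as d/2), correlation 0.5, 21 per arm. The noncentrality is d × sqrt(21/2) / s, where s² is the variance of the outcome after any adjustment, with each rating scaled to variance 1.

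- One time point adjusted for t1: s² = 1 − 0.5² = 0.75, noncentrality 1.87, df 39. Power is 45%, or 24% at alpha 0.0125.
- Mean of t4, t6 and t8, unadjusted: s² = (1 + 2 × 0.5)/3 = 0.667, noncentrality 1.98, df 40. Power is 49%.
- Mean of t4, t6 and t8 adjusted for t1: s² = 0.667 − 0.25 = 0.417, noncentrality 2.51, df 39. Power is 69%.

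Over correlations 0.3 to 0.7 the last figure runs from 66% to 81%. With 17 per arm and correlation 0.5 it is 59%.

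**The case against.** The strongest reply is that a multiplicity method is commonly settled in an analysis plan, and that plan is not shown. This stands as far as timing goes: choosing the method after the protocol is not in itself a fault. It does not answer the main point, because the protocol itself frames the primary test as several comparisons and makes correction optional.

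Four stronger readings are tempting, and the documents do not support them.

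- *The baseline is tested as a primary result.* The list taken literally includes t1, which precedes stimulation. But the outcome is defined as change from baseline, so t1 is better read as the reference. A five-test error rate should not be quoted.
- *The analysis is no more than separate t-tests, in which a person-level random effect cannot be estimated.* That follows only from one sentence in Outcomes {12}. The Abstract and Statistical methods {20a} describe a joint model over the repeated measures. A joint model that reports an effect at every time point has the same multiplicity, so the finding does not need this claim.
- *FDR leaves the error rate uncontrolled.* With no effect anywhere it stays below 5% (step 3). Its weakness is narrower: familywise control is not guaranteed once some effects are real.
- *One contrast raises power from 17% to 69%.* The 17% is a Bonferroni-corrected time point without baseline adjustment, so that comparison mixes two changes. Much of the gain comes from adjusting for baseline, and {20a} already contemplates baseline covariates. Moreover, the chance of at least one significant baseline-adjusted result under Bonferroni over four is about 48%, against 67% for the average (simulation, 4,000 runs, no effect at the neutral video).

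**Conclusion.** The concern holds in this form: the protocol names no single primary contrast or success rule, includes a neutral-video comparison that does not bear on reactivity, leaves correction optional, and is sized for one test at 0.05. If no correction is applied, the false-positive rate for the primary claim is about 13% to 17% over four ratings or 11% to 14% over the three negative videos, at least twice the nominal 5%. That size depends on 17 per arm, equal correlations of 0.7 to 0.3, and no correction being made. The protocol permits the last of these but does not prescribe it. The power figures further assume d = 0.5 at each negative video. The absence of a single primary test does not depend on any of these assumptions.

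**What to change.** Before anyone sees outcomes by arm, rewrite Outcomes {12} and Statistical methods {20a} to name one primary test at two-sided 0.05: the taVNS-sham difference in PANAS-N averaged over t4, t6 and t8, adjusted for t1, from one joint mixed model. State that t1 is not tested and that t3 serves only as a control condition. Report each negative video as secondary, with a confidence interval. Align Sample size {14} with this contrast and state the correlation assumed. On the assumptions above, power falls short of the planned 80% unless the correlation is about 0.7, and the protocol should say so.

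Other single procedures, such as one joint group-by-time test or Holm over named contrasts, would also control the error. The average is suggested because it addresses reactivity directly and does not split alpha.

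The cost is revised wording and a registry update. Formal claims at single videos are given up, and an effect confined to one video would be diluted in the average. No extra participants are needed to make the change.

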The neutral video depicts a mother attempting to show a father that their young son can play chess and elicited very low levels of emotions in an undergraduate sample [72]. The three negative clips depicted a scene of domestic abuse between a man and a pregnant female partner; a funeral scene where a young girl struggles with the death of her friend; and a scene involving sexual assault by a police officer toward a woman while her husband watches. The domestic abuse clip significantly increased negative mood in a community-sourced sample [73]. The funeral clip elicited sadness in an undergraduate sample, whereas the sexual assault clip elicited anger, disgust, and contempt [72].

The titles and years of production of the films from which the videos are taken are *Searching for Bobby Fischer* (1993; neutral), *Nil by Mouth* (1997; domestic violence), *My Girl* (1991; funeral), and *Crash* (2004; sexual abuse).

After every post-induction period, for the three emotion-inducing videos, the participants will have other 90 seconds to rate again the PANAS (recovery ratings) (see Table 1). The neutral video will be always presented first to allow participants to orient themselves to the procedure. The three affect-evoking videos will be instead presented in a random order using the “randomizer” function of a Qualtrics software [74] (see below). Each page will be locked with a visible timer to ensure that all participants will progress through the procedure at the same pace. If a participant finishes the questions in advance, he/she will be instructed to sit quietly until the next page appears.

At the end of the survey, participants will answer additional questions on the quality of their participation (PQE).

All the instructions, questions, videos, and rating scales will be administered through an online Qualtrics survey [74], with time-fixed auto-advance according to the protocol-defined exposition time for every step of the experiment (see Table 1).

The software IMotions [75] will be used to integrate the data collected from the Qualtrics Survey and from the ECG and GSR sensors.

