### Sample size {14}

We are going to recruit 42 participants (21 participants per arm). The total sample size has been calculated using G*Power 3.1 Software to test an effect size of 0.25 with a power (1−*β*) = 0.8 for a sample with two independent groups (taVNS vs Sham-taVNS) and 4 dependent measures (PANAS-N score post-induction for neutral, funeral, sex-assault and domestic violence videos). The sample size needed is *n* = 34, calculated with an alpha level of 0.05. With an expected level of attrition of about 20%, the sample size has been increased by a factor of 1/(1–0.2) = 1.25 or 25% to 42 subjects.

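### The three negative clips are shown in random order but clip is not among the named model terms, so the comparisons at t4, t6 and t8 lose some precision

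*Protocol article*

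**What the plan says.** **Order of clips.** Intervention description {11a} fixes the neutral clip: "The neutral video will be always presented first to allow participants to orient themselves to the procedure". For the others: "The three affect-evoking videos will be instead presented in a random order". The order comes from a function of the survey software. The section does not say whether that function balances the orders, within arm or overall.

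**Unit of analysis.** Outcomes {12} takes the primary ratings at baseline, after the neutral clip and "after each of the three affect-inducing videos (designated as t1, t3, t4, t6, and t8 in Table 1". It then states: "A mixed model analysis will be employed to assess each time point separately, ensuring comprehensive evaluation across all time points". Recovery uses t4 to t9, and PEME uses t3, t4, t6 and t8.

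**Model.** Section {20a} describes mixed models with a random effect for the individual, baseline covariates to be considered, and fixed effects as follows: "with treatment group, treatment state, and time entered as fixed effects to estimate the effects stemming from the sham/intervention at each time point". Neither clip nor order of presentation is named, and treatment state is not defined.

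**Sample size.** Section {14} counts "4 dependent measures (PANAS-N score post-induction for neutral, funeral, sex-assault and domestic violence videos", which indexes the repeated measure by clip.

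**The concern.** With a random order, clip and time point are two different factors. The rating at t4 follows the funeral clip for some women, the domestic abuse clip for others and the sexual assault clip for the rest. {11a} reports that these clips evoked different emotions in earlier samples. If they also differ in how far they raise negative affect, a comparison of arms at t4 that ignores clip carries the between-clip variance in its error. By chance, one arm may also contain more women who saw the strongest clip at that point.

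What is at stake is precision in the primary post-induction comparisons and in PEME, in a trial with 21 women per arm. There is also a plain inconsistency: the power statement describes measures by clip, while the outcome and model sections describe them by time point.

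**Working it through.** **1. The plan's own figure.** Inputs from {14}: effect size 0.25 (taken as Cohen's f), power 0.80, alpha 0.05, two groups, four measures. For a between-group test, λ = f²·N·m / (1 + (m − 1)ρ). With ρ = 0 and N = 34, λ = 0.0625 × 34 × 4 = 8.5 and power is 0.807, so 34 is reproduced. The group-by-measure interaction, λ = f²·N·m / (1 − ρ), also comes close: power is 0.799 at N = 34 with ρ = 0.25. The article states neither the test nor ρ. Attrition: 34 × 1.25 = 42.5, given as 42. Neither formula has an input for clip or position variance, so this point does not alter the stated N.

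**2. Clip or position?** The labels run: t1 baseline, t2 pre-induction, t3 neutral clip, then post-induction and recovery in turn (t4/t5, t6/t7, t8/t9). That is chronological order. Because the clip order is random, a chronological label does not identify a clip.

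**3. Added variance at one position.** Assumptions, none of them in the article: within-clip PANAS-N SD 8; clip means equally spaced at −D, 0 and +D; each clip equally likely at each position. The effect is d = 2f = 0.5, which is 4 points at SD 8. Clip variance is 2D²/3. Power is from the noncentral t with 40 df and noncentrality d·√(21/2).

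| Spread 2D (points) | Clip variance | Total variance | Increase | Effective d | Power |
|---|---|---|---|---|---|
| 0 | 0 | 64 | 0% | 0.500 | 35.3% |
| 6 | 6 | 70 | 9% | 0.478 | 32.7% |
| 10 | 16.7 | 80.7 | 26% | 0.445 | 29.1% |
| 14 | 32.7 | 96.7 | 51% | 0.407 | 25.1% |

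**4. Effect of a clip term.** Simulation of one position (6,000 runs per setting, 21 per arm, within-person correlation 0.5), with D in within-clip SDs:

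| D | Power without clip | Power with clip |
|---|---|---|
| 0 | 35.1% | 33.8% |
| 0.25 | 34.3% | 33.5% |
| 0.5 | 31.5% | 34.7% |
| 1 | 22.8% | 34.1% |

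With no true effect, rejection rates stayed between 4.2% and 5.3%, with or without the term.

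**5. Chance imbalance.** At a 10-point spread, the arm difference in mean clip level at one position has mean 0 and SD √(2 × 16.7/21) = 1.26 points. The ordinary standard error is 8 × √(2/21) = 2.47. Together they give √(1.26² + 2.47²) = 2.77, and (2.77/2.47)² = 1.26. That is the same 26% as in step 3, so imbalance and added variance are one quantity seen twice. If the randomizer is unrestricted, the number seeing a given clip at a given position is Binomial(21, 1/3) in each arm. The arms then differ by 4 or more with probability 25.1%, and by 5 or more with probability 13.9%.

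**6. Where it does not apply.**
- t1 and t2 precede every video, and t3 always follows the neutral clip.
- Averaged over the three negative clips, a completer's clip contribution is (−D + 0 + D)/3 = 0. Simulated power for that mean was 48.1% to 50.1% for D from 0 to 1, with no trend.
- A recovery change (t4 to t5, and so on) compares two ratings after the same clip. Clip level cancels unless clips differ in recovery.
- PEME is one rating per clip, so it has the same structure as the post-induction ratings. It was not calculated, because its scale differs and no SD is given.

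**The case against.** Table 1, which defines the time labels, is not shown, and {14} speaks of clips, so t4, t6 and t8 could be clip labels. {20a} does not say that its list of fixed effects is complete, and an analysis plan may add to it. This does not remove the point. The chronological reading is the likelier one; if the labels do mean clips, position in the session becomes the unmodelled factor. On either reading {14} and {12} need to be reconciled.

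The size is open to a stronger challenge. {11a} describes the clips by kind of emotion, not by strength, and the section on self-reported ratings says that the PANAS rates mood states instead of discrete emotions. Clips that evoke different emotions may therefore give similar PANAS-N totals, and the loss may be a point or two of power. That stands.

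A reader might infer that chance imbalance biases the trial, or that a surplus of 4 women out of 21 could shift a comparison by 10 × 4/21 = 1.9 points, nearly half of a 4-point effect. That shift needs the surplus on the strongest clip to be matched by a deficit on the mildest. Under the same 10-point assumption, a shift that large has probability 16%, not 25%, and the test's standard error already allows for it. A reader might also infer that the order is unbalanced; the article does not say either way.

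**Conclusion.** The point holds in limited form. Under the chronological reading, clip differences enter the error of the per-time-point post-induction and PEME comparisons at t4, t6 and t8. The cost is precision; type I error stays near 5%. Assuming SD 8, a 4-point effect and 21 per arm, power at one position falls from about 35% to 33%, 29% or 25% at assumed spreads of 6, 10 or 14 points, and a clip term restores about 34–35%. The spread is not in the documents, so none of these losses can be called the expected one.

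It would be wrong to extend this to every time-point comparison: t1, t2 and t3 are untouched, and recovery changes are affected only if clips differ in recovery. The mean over the three negative clips is unaffected in completers. That cancellation is no longer exact where a missing rating is filled with the mean of the others, as {20c} provides, because those follow other clips. Power of about 35% at one position with no clip effect at all is a larger limitation than the missing term.

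**What to change.** In Outcomes {12} and section {20a}, state that the joint post-induction, recovery and PEME models include both clip identity (domestic abuse, funeral, sexual assault) and position as fixed effects. Position is already there if time means session position. The neutral clip occurs only at t3, so clip needs just two contrasts among the three negative clips. In {14}, define the repeated measures in the same way as the analysis, and say in the text whether t4 to t9 are positions.

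The cost is two model degrees of freedom and a few sentences. No new data are needed, because the survey controls which clip is shown when. The order assignment need not change during recruitment: the simulations recover the lost power with unrestricted orders once clip is in the model.
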